**Abstract:**

The aim of this study is to test the cost-effectiveness and cost-utility of adding a transdiagnostic group cognitive-behavioural therapy (TD-CBT) to treatment as usual (TAU) for emotional disorders in primary care . A single-blind randomized controlled clinical trial will be conducted to compare the TD-CBT group therapy plus TAU to progressive muscle relaxation (PMR) group plus TAU in individuals, aged 18 to 65, with emotional disorders in four primary care centres located in Cantabria, Spain. The study will take a societal perspective. Psychological assessments will be carried out at baseline, post-treatment, and 12-months follow-up. The assessments will include measures of clinical symptoms (anxiety, depression, and/or somatic), dysfunction, cognitive-emotional factors (ruminative processes, pathological concern, attentional and interpretative biases, emotion regulation strategies and meta-cognitive beliefs), and satisfaction with the treatment received. Data on health service use, including medication and days of absence from work, will be collected from electronic medical records. The primary outcomes are the incremental cost-effectiveness ratios (ICER) based on the difference in mean costs and effectiveness between interventions and incremental cost-utility ratios (ICURs) based on health-related quality of life at post-treatment and 12-month follow-up. Secondary outcome measures include clinical symptoms, quality of life, functioning and treatment satisfaction. Bootstrap sampling will be used to assess the uncertainty of the results. Secondary moderation and mediation analyses will also be conducted. In addition, in sessions' number 1, 4 and 7 of both treatment arms, two questionnaires will be administered that collect therapeutic alliance and group satisfaction. The main study hypothesis is that adding TD-CBT to TAU in primary care will be more cost-effective than TAU plus PMR. In addition, these gains will be maintained in the 12-month follow-up. If it is successful, the dissemination of cost-effective treatment can help to overcome problems in accessing psychological treatment for emotional disorders in the context of an increasing demand for mental healthcare in primary care.

**Pathologies:**

Emotional disorders (depression, anxiety and somatoform disorders)

**Key words:**

transdiagnostic therapy

progressive muscle relaxation

emotional disorders

primary care

cost-effectiveness analysis

cost-utility analysis

brief psychological treatments

cognitive behavioural therapy

randomized controlled trial

depression

anxiety

somatoform disorders

**BACKGROUND AND CURRENT STATUS OF THE TOPIC AND BIBLIOGRAPHY**

**The extent of mental disorders**

Epidemiological studies in Spain indicate that around 1 in 5 people will present a mental disorder during their lifetime [1] and 8.4% during the last 12 months. Anxiety disorders (6.2%) and mood disorders (4.4%) are the most frequent in the last 12 months [1]. In Cantabria, the point prevalence in some epidemiological studies is 14.7%. [2] In the case of Primary Care (PC) health centres, it can be estimated, based on the different epidemiological studies in our environment, that around 30-35% of the people they attend have a mental disorder. At this level of care, anxiety disorders are the most frequent, followed by depressive disorders. [3]

**The cost of common mental disorders**

In developed countries, 38% of illnesses are mental disorders [4], particularly affecting people of working age where they account for 50% of all illnesses. Recent studies in Europe rank mental disorders as the leading cause of loss of quality of life expressed as Disability Adjusted Life Years (DALYs) and as the main reason for disability pension claims. [5] In Spain, mental disorders are the second most frequent cause (after diagnoses of osteo-muscular origin) of temporary incapacity (TI) processes managed by PC physicians. Moreover, according to data from Cantabria, more than 80% of the diagnoses included in mental health TI reports correspond to "neurotic" or "minor" disorders. [6] Paradoxically, the mental disorders with the best prognosis (i.e. those related to anxiety, depression and adaptive disorders) are one of the main sources of expenditure for TI benefits, as they combine two characteristics: high frequency and very long duration. [7]

The economic costs of mental disorders were estimated for 2010 in the European Union at €461 billion, excluding the costs of dementia and neurological disorders; the main part of this figure corresponds to indirect costs linked to lost productivity and disability pensions. [8] In Spain, the social cost of mental disorders (excluding dementia and other neurological disorders) accounted for 46 billion euros in 2010, with anxiety-related disorders and depression, at more than 10 billion each, accounting for the largest shares of this expenditure. [9]

These costs are underestimated because they do not take into account, among other things, the effect of comorbidity of mental disorders on people with physical illnesses. For example, people with chronic physical illnesses (asthma, cancer, COPD, arthritis, hypertension, diabetes, heart attacks and heart problems) with comorbid anxious-depressive disorders have an average monthly medical expenditure between 33-169% higher than the average for these illnesses, excluding out-of-pocket costs for mental health services. [10] Moreover, mental disorders increase the risk of developing some physical illnesses. [11] People with depression have an increased risk of developing a heart problem; after a heart attack, each additional depressive symptom that develops increases the risk of another heart attack by 15%. [12]

Excess mortality is well established among patients with mental disorders compared to the general population. [13,14,15] In particular, the risk of suicide is increased for all mental disorders, not only for the most severe disorders, but the adaptive disorders, a residual, quintessentially mild diagnostic category, have a suicide risk more than 10 times that of the general population. [16] Psychological autopsies indicate that around 90% of suicides have a mental disorder as the main motive. [17] In Spain, suicide is the most likely cause of death for a man aged 20-49. Taking the figures as a whole, the number of deaths from suicide per year, 3,870 people in 2013, are higher than those from traffic accidents, falls, murder or drugs. [18] Finally, it has been noted that contact with PC professionals in the time prior to suicide is common; however, although three out of four suicide victims had contact with PC professionals within a year of suicide, only a third of victims had had contact with mental health services. [19]

**Mental disorders are undertreated, late and mistreated**

A review of epidemiological data drawn from 27 studies involving 150,000 people from 16 European countries highlighted, in addition to the large size and range of psychosocial disturbances associated with mental disorders, that mental disorders have a relatively low rate of treatment. Only 26% of all cases with mental disorders had had formal health care consultations for mental health reasons in the last month. [20] Among treated cases with mental disorders, there was a long delay between onset of the disorder and first contact for treatment and only a small number of patients received minimally adequate intervention. [21]

**The efficacy of cognitive behavioural therapy**

Several meta-analyses have shown that CBT is effective for common mental disorders, such as anxiety and depression. Large effect sizes have been found for disorders such as unipolar depression, generalised anxiety, panic disorders with or without agoraphobia, social phobia or post-traumatic stress disorder. [22] In the case of depression, CBT, the most widely researched form of psychotherapy, a recent meta-analysis found a moderate-large effect size (Hedges g = 0.71), which corresponds to a number needed to treat (NNT) of 2.6.

There is strong evidence that the efficacy of psychological therapy and CBT in particular is equal or greater than pharmacological treatments for the most common affective and anxiety disorders, as well as having greater long-term effectiveness. [22,24-25] In particular, the benefits of psychological approaches include a reduction in symptoms associated with anxiety and depression, a decrease in the risk of relapse, stability of long-term treatment effect, and high rates of recovery, prevention of chronicity and decreased health costs, in terms of medical consultations and medication use, as well as sick leave. [26]

In the case of research on the effectiveness of CBT in the PC setting, although the number of studies is smaller, a recent meta-analysis showed that CBT-based treatment for depressive and anxiety disorders is more effective than no treatment (d =0.59) and treatment as usual in PC (d = 0.48). [27] Of note, there is substantial evidence that psychological treatments using the CBT approach in depressed patients in PC treated with less resource-intensive interventions achieve similar outcomes to those of more intensive treatments. [28] This is especially relevant in view of the fact that CBT-based group treatment may be a particularly cost-effective modality. A meta-analysis of 32 studies of adults with depression found that after the intervention depression levels were significantly reduced with a moderate effect size (g=0.40) compared to controls, and these results were maintained at 6-month follow-up. [29] The typical format in the included studies was groups of 6-10 participants, with 1-hour therapy extending over 2-8 weeks. Similarly, research in 14 studies with psychological group therapy in PC (n = 1,217), comparing treatment as usual in PC with psychological group therapy plus treatment as usual, has shown clinical improvement with a considerable effect at the end of treatment (d = 0.55). [30] Research in this field in Spain is scarce. Some studies point to the efficacy of group psychological interventions based on CBT in PC for depression in both the short and long term [31], and also in the case of anxiety disorders. [32] Although the methodological weaknesses of these studies make it necessary to be cautious with the interpretation of the results.

Based on the results of extensive research on the effects of psychological treatments, the *National Institute for Health and Care Excellence* (NICE) guidelines recommend the use of psychological treatments, particularly CBT, in PC before pharmacological treatments for mild and moderate major depression, generalised anxiety disorder, post-traumatic stress disorder, obsessive-compulsive disorder and panic disorder (i.e. for the most common mental disorders). [33]

Clinical guidelines emphasise the conjunction of empirical evidence with patient values and preferences in the selection and application of treatments. Patients with mental disorders as a whole show a 3-fold greater preference for psychological than pharmacological treatment. [34] A recent meta-analysis states that pharmacological treatment is 1.76 times more likely to be refused and 1.20 times more likely to be abandoned than psychotherapy [35] In this regard, it is relevant to note that patient preferences can directly affect therapy outcomes; there is growing evidence that providing patients with their preferred treatment is associated with greater adherence and better clinical outcomes. [36] Thus, it has been observed that when PC patients with depression received their preferred treatment, their recovery as measured by the HAMD-17 depression scale increased significantly: +2.9 points for pharmacological treatment and, in the case of group CBT, by +8.0 points, which should be considered clinically significant. [37]

**A novel approach to the treatment of mental disorders - the transdiagnostic model**

Although research has demonstrated the effectiveness of psychological treatments for common mental disorders, only a small proportion of those suffering from these mental disorders receive them. Several reasons have been put forward for the underuse of psychological treatments, such as stigma, lack of training of professionals in psychological treatments or, among other reasons, the multiplicity of treatment protocols for different disorders, which often have significant comorbidity, making it difficult for the clinician to decide which protocol to follow. The high rates of psychiatric comorbidity, which in some disorders are above 80% [38], the difficulty in delimiting specific aetiologies for the more than 400 mental disorders listed in diagnostic manuals, and the questionable validity of these manuals have given rise to new proposals for classification and intervention based on transdiagnostic models [39]. This perspective assumes that different emotional disorders share important characteristics and proposes that this overlap emerges from common biological and psychological vulnerabilities that, associated with psychosocial stressors, may result in different manifestations of the same vulnerability. [40] The transdiagnostic perspective emphasises the role of emotion regulation as a key concept for understanding and treating emotional disorders. The concept of emotion regulation refers to the strategies that people engage in to modify the emotional experiences they undergo. Inappropriate emotion regulation strategies such as rumination and avoidance have been found to play an important role in the onset and maintenance of anxiety and depressive symptoms prevalent in common mental disorders. [41] The transdiagnostic model draws on the contributions of cognitive-behavioural theories to incorporate common principles of empirically supported treatments, namely, re-evaluation of negative interpretations, modification of maladaptive behaviours, prevention of emotional avoidance, and use of emotional exposure procedures for feared situations and re-activation of behaviour in low mood. [42] These mechanisms have been shown not only to change behaviour and emotional experience, but also to produce changes in brain function. [43]

**Programmes to facilitate access to psychological treatments**

Based on the above evidence, facilitating access to psychological treatments has become a priority. It is worth highlighting the initiative launched by the UK government in 2007 to offer CBT-based treatments for the most common mental disorders in the PC setting (mainly anxiety and depression), in accordance with the recommendations of NICE guidelines. [44] The programme was called Improving Access to Psychological Therapies (IAPT) and has been the largest effort to date worldwide to disseminate evidence-based psychological treatments to the general population through PC services. Previously, two pilot projects were run for 13 months with clinical outcomes that largely met expectations. [45,46] A large number of patients with these disorders were treated with low-intensity interventions (including different group treatment modalities), which is particularly useful for achieving high cost-effectiveness. At initial assessment, 55-56% of patients who had attended at least two sessions, including the assessment interview, were classified as recovered when they left services, and treatment gains were largely sustained at 10-month follow-up. At further evaluation, effect sizes of d=1.39 for anxiety problems and d=1.41 for depression problems were achieved. In addition, high recovery rates (76% for depression and 74% for anxiety), decreased risk of relapse and maintenance of positive long-term outcomes were achieved. [46] Of the patients who completed the course of treatment in IAPT, 45% recovered (based on a strict dual-criterion, score below the clinical threshold for anxiety and depression), and an additional 16% showed improvement just below full recovery. [47]

**The situation in Spain with regard to the treatment of mental disorders**

A similar initiative to disseminate evidence-based psychological treatment has not been developed in Spain, despite the fact that 65% of people diagnosed with a mental disorder in the last twelve months have not received any health treatment in the last year [48] and the burden of mental illness is greater than that of physical illness and its onset precedes physical illness. [49] Although almost 60% of people with mental disorders visit their GP, psychological treatment is not usually provided in this setting, so this type of treatment only reaches a small percentage of patients, who are referred to Specialised Care Services (Mental Health).

The proportion of cases diagnosed with an anxiety or mood disorder in the last twelve months that receive minimally adequate treatment according to scientific evidence is low, being only 31.8% in specialised care (10.8% in the case of psychological treatment) and 30.5% in PC [50] (the lowest percentages among the countries in our environment). Similarly, psychological treatment is applied to only 0.9% of cases with an anxiety disorder in the last twelve months [48], despite being the treatment of choice [34]; 27% of these patients receive psychological and pharmacological treatment, while 33% receive exclusively pharmacological treatment and 39% of the minority with mental disorders who come to consult health services do not receive any treatment for this type of disorder. [48]

Different factors may explain this situation, such as the training of professionals, the time required, the overload of care, the attitudes of professionals or the organisation, or the relationship between PC and specialised care. What is certain is that empirically supported treatments involve sessions of at least 1 hour and with a weekly or fortnightly frequency, at least initially. These characteristics exceed the resources that GP have to care for their patients. This explains the tendency to use pharmacological treatment as almost the only therapeutic option, even in cases where it is not the treatment of choice, it is not the patient's preference among the available treatments or the patient has not responded favourably to it in a first attempt. In this line, the Mental Health Strategy of the National Health System recognises that the marked tendency to over-medicalise mental health, including disorders that should be treated with psychological treatments. [51]

Overall, we have a situation in Spain, and in Cantabria in particular, in which there is a health problem with a high prevalence, which causes significant costs for the affected person, their relatives and for society as a whole. However, despite the existence of appropriate psychological therapies recommended by the reference clinical guidelines as the treatment of choice for the most prevalent mental disorders (i.e. those based on CBT), they are hardly used at the level of care through which the health system is accessed and where most of these health problems are treated: PC. Although there are some initiatives worldwide to facilitate access to psychological treatments, in Spain there are no rigorous methodological studies to prove their cost-effectiveness in the PC context. Particularly relevant is the study of treatments that allow their application in formats and approaches that can be easily disseminated in health centres, as is the case of short-term transdiagnostic group treatments.

**Primary purpose:**

Test cost-effectiveness and cost-utility of transdiagnostic cognitive-behavioural treatment versus relaxation therapy in Cantabria Primary Care Centres at posttreatment and 12-month follow-up.

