**Outcome Measures**

Primary Outcome Measures:

- Change in cost-effectiveness data [Time Frame: Baseline, immediately after the intervention, and 12-month follow-up]

Cost-effectiveness results will be calculated by the ICER, defined as the difference in mean costs between interventions divided by the difference in their effectiveness according to the symptom questionnaires’ mean scores.

The healthcare data collected will be used for cost calculations. To calculate healthcare-related costs, an ad hoc questionnaire will be used to collect emotional disorder-related healthcare data (public and private healthcare consultations, accidents, medical tests, and sick leaves in the past 3 months; psychotropic drugs or other medication, and their posology).

- Change in cost-utility data [Time Frame: Baseline, immediately after the intervention, and 12-month follow-up]

Cost-utility will be measured through the healthcare data collected above and the European Quality of Life Scale (EuroQoL, EQ) [71], calculating the QALYS and the ICURs, defined as the difference in mean cost divided by the difference in mean QALYs. The Spanish version of the 5-domain, 5-level EuroQol (EQ-5D-5L) [72,73] will be used to assess health status in five dimensions (mobility, self-care, daily activities, pain/unease, and anxiety/depression) with five levels of severity (no problems, slight problems, moderate problems, severe problems, and either extreme problems or unable to perform activity). The scores obtained in the different dimensions can be combined to create a 5-digit code describing the patient's state of health, being able to stablish up to 3125 different combinations, and therefore, different possible health states. This system was converted into a utility score using the value set for Spain from the EQ-5D-5L Crosswalk Index Value downloaded from the EuroQol website (<https://euroqol.org/euroqol/>).

Secondary Outcome Measures:

- Change in depressive symptoms: Patient Health Questionnaire - 9 item (PHQ-9) [Time Frame: Baseline, immediately after the intervention, and 12-month follow-up]

The PHQ-9 [54] is the depression module of the PHQ [74, 75] that scores the 9 DSM-IV depression criteria in the last two weeks. Is a nine item, self-report scale that ranges from 0 to 27 (higher scores means a worse outcome).

- Change in anxiety symptoms: Generalized Anxiety Disorder - 7 item (GAD-7) [Time Frame: Baseline, immediately after the intervention, and 12-month follow-up]

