**APPLICABILITY AND USEFULNESS OF THE RESULTS AND ABILITY TO BE PROTECTED AND TRANSFERRED TO THE MARKET**

The planned clinical trial will provide clear evidence that, compared to treatment through relaxation, the incorporation of a group treatment for mental disorders commonly treated in Health Centres helps to reduce anxious, depressive and somatic symptomatology, as well as a reduction in the costs (direct and indirect) associated with anxiety, mood and somatoform disorders (Main hypothesis). PsicAP-Costs2 allows an immediate transfer of the results to the clinical context by providing the first experience in our context of a manualised transdiagnostic group treatment of short duration (7 sessions), which makes it easily applicable and generalizable to health centres in Cantabria and the rest of the NHS. The expected economic benefit in the reduction of psychopharmacological treatment costs and through the reduction of expenditure on sick leave and loss of productivity, which is a priority objective of the SCS in the management of TI associated with common mental disorders (Mental Health Plan of Cantabria 2015-2019), should make the dissemination among health professionals of this type of protocolised treatment, low cost and short duration, easily integrated into the routine care offered in Health Centres, profitable.

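### The main hypothesis rests on four to eight unranked primary ratios at two horizons, and its two wordings can be answered differently by a better but dearer TD-CBT

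*Protocol*

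**What the plan says.** The Primary purpose reads: "Test cost-effectiveness and cost-utility of transdiagnostic cognitive-behavioural treatment versus relaxation therapy in Cantabria Primary Care Centres at posttreatment and 12-month follow-up". It covers two analyses, cost-effectiveness and cost-utility, each at both times.

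Outcome Measures lists both as primary, each with baseline, post-intervention and 12-month time frames. The ICER is "the difference in mean costs between interventions divided by the difference in their effectiveness according to the symptom" questionnaires. Its effect measure is "symptom questionnaires’ mean scores", in the plural, and no scale is singled out. Three symptom scales appear among the secondary outcomes: PHQ-9, GAD-7 and PHQ-15. The cost-utility outcome is obtained by "calculating the QALYS and the ICURs, defined as the difference in mean cost divided by the difference in mean QALYs".

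The Abstract repeats the pairing, with "incremental cost-utility ratios (ICURs) based on health-related quality of life at post-treatment and 12-month follow-up" beside the ICER. The Statistical analysis section defines the ICER again, without a scale or a time point.

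The main hypothesis appears twice. The Abstract says: "The main study hypothesis is that adding TD-CBT to TAU in primary care will be more cost-effective than TAU plus PMR". Its next sentence adds that the gains will last to 12 months. The Applicability section attaches the label of main hypothesis to the claim that the group treatment "helps to reduce anxious, depressive and somatic symptomatology, as well as a reduction in the costs (direct and indirect"), and presents this as something the trial is going to show.

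No section names a deciding ratio, a rule for discordant ratios, or a willingness-to-pay threshold.

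**The concern.** One main hypothesis should have one result that settles it, fixed before the data are seen. Here several primary ratios stand on one level, and the hypothesis has two wordings that do not mean the same. The report could then rest on whichever scale, horizon or wording is most favourable, and the protocol would not contradict it.

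A statistical analysis plan may exist, but that does not remove the point. Which outcome and time point decide the main hypothesis is a matter for the protocol, and this protocol does address it, without settling it.

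The two horizons also need care. A QALY difference is an area under a curve and grows with follow-up, while some costs fall early. The post-treatment and 12-month ICURs are therefore answers to different questions, not two readings of one quantity.

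**Working it through.** **Count of ratios.** Each horizon has one ICUR. It also has one ICER if a single symptom measure is used, or three if each scale has its own. With two horizons the total is (1 + 1) × 2 = 4 up to (3 + 1) × 2 = 8.

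**The two main hypotheses side by side.**

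| Result for TD-CBT against PMR | Abstract: more cost-effective | Applicability: fewer symptoms and lower costs |
|---|---|---|
| Better and cheaper | Met | Met |
| Better and dearer | Met if the extra cost per unit of effect is acceptable | Fails |

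The second row is the conflict. It needs no numerical assumption.

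**Effect of the horizon on the ICUR.** The protocol gives no expected cost, utility gain or ratio, so there is no figure of its own to reproduce. Inputs:

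- Post-treatment at week w = 12 (Description of the type of trial; Name of each arm) or w = 24 (the two sections describing the treatments). The document contradicts itself here, so both are used.
- 12 months taken as T = 52 weeks from baseline. The protocol does not state the starting point.
- Assumed: the utility difference rises linearly from 0 to du at week w and then holds to T. Holding follows the Abstract's prediction that gains are maintained.
- Assumed for illustration: du = 0.05 and incremental cost C = EUR 100, positive.

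Formulas:

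- QALY gain at post-treatment = du × 0.5w / 52
- QALY gain at 12 months = du × (0.5w + T − w) / 52
- ICUR = incremental cost to that time / QALY gain to that time

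QALY gains:

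- w = 12: 0.05 × 6/52 = 0.0058 and 0.05 × 46/52 = 0.0442
- w = 24: 0.05 × 12/52 = 0.0115 and 0.05 × 40/52 = 0.0385

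*All extra cost early.* C is the same at both times, so the ratio of ICURs is the inverse ratio of QALY gains:

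- w = 12: EUR 17,333 against EUR 2,261 per QALY; factor 46/6 = 7.67
- w = 24: EUR 8,667 against EUR 2,600 per QALY; factor 40/12 = 3.33

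*Extra cost accruing evenly to 12 months.* Cost at post-treatment is C × w/52, so the post-treatment ICUR is 2C/du = EUR 4,000 for either w:

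- w = 12: EUR 4,000 against EUR 2,261; factor 2 × 46/52 = 1.77
- w = 24: EUR 4,000 against EUR 2,600; factor 2 × 40/52 = 1.54

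The factors do not depend on du or C. If 12 months is counted from the end of treatment instead, they are 9.67 and 1.81 (w = 12; early and even cost), or 5.33 and 1.68 (w = 24).

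*Where the factor vanishes.* It is 1.0 if cost and QALY gain both accrue at a constant rate from day 0. It is also 1.0 if cost accrues evenly and the utility gain fades linearly to zero at 12 months. If TD-CBT is cheaper and better at both times, both ICURs give the same verdict at any threshold.

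**When verdicts differ.** With positive extra cost and a positive QALY gain, the two horizons disagree only if the threshold lies between the two ICURs. For w = 12 in this illustration, that is between EUR 2,261 and EUR 17,333 with early cost, or between EUR 2,261 and EUR 4,000 with even cost.

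**The case against.** The strongest reply is that the large factors need a positive extra cost that falls entirely early. Both arms receive seven 1.5-hour group sessions from psychologists, in groups of similar size, so session costs largely cancel. Consultations, drugs and sick leave accrue over time. This stands, and it makes the 1.5- to 1.8-fold range as relevant as the larger one.

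A reader might infer that the choice of horizon alone reverses the trial's conclusion. The documents do not support that. A different ratio is not a different verdict until it is set against a threshold, and none is stated.

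A reader might also infer that up to eight primary ratios inflate the false-positive rate by a calculable amount. The protocol plans no test per ratio and describes bootstrap sampling for uncertainty, so no such rate can be assigned.

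It can also be said that cost per symptom point and cost per QALY are complementary estimates, and that the Abstract offers a partial order: a main hypothesis first, durability at 12 months second. Both are fair. But that order names no measure and does not say which horizon prevails if they disagree.

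Finally, the Applicability section describes expected benefit and is not the objectives section. It nevertheless uses the label of main hypothesis for a stricter claim, so the conflict stays.

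**Conclusion.** The point holds as one of ranking and wording. Four to eight primary ratios carry the main hypothesis and none decides. The two versions of that hypothesis part company for a better but dearer TD-CBT. These two conclusions rest on the text alone.

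The size of the horizon effect is conditional. Given a utility gain reached linearly by post-treatment and then held, positive extra cost, and 12 months counted from baseline, the post-treatment ICUR exceeds the 12-month one by 7.7-fold or 3.3-fold (week 12 or 24) with early cost, and by 1.8-fold or 1.5-fold with even cost. It can disappear under other profiles. This shows that the two ICURs should not share primary rank. It does not show that the trial's conclusion would change. The sponsor should correct this; the data to be collected are not at fault.

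**What to change.** In the Abstract, Primary purpose and Outcome Measures, name the ICUR over baseline to 12 months as the result that decides the main hypothesis. Report the post-treatment ICUR and the symptom-scale ICERs as secondary or supportive. A single named symptom ICER would also be a defensible choice. The 12-month ICUR has the advantage that it uses one utility measure already planned and covers the period over which gains are expected to last.

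In the Applicability section, replace the text labelled as main hypothesis with the Abstract's version, list symptom reduction and cost reduction as secondary hypotheses, and say that the trial will test whether these occur.

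Two contradictions must be reconciled alongside this. The treatment period is 12 weeks in some sections and 24 in others. The Chronogram recruits in months 2 to 11 and completes data collection and analysis in months 10 to 12, yet a patient enrolled in month 2 reaches 12 months only in month 14 (2 + 12), and one enrolled in month 11 in month 23 (11 + 12). The protocol should also make clear that the medical records cover the months outside the cost questionnaire's 3-month recall.

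The ranking and the hypotheses need wording changes only, with no new data. A 12-month primary result does depend on a timetable that can hold it. The downside is that an early post-treatment or single-scale result can no longer be presented as the primary answer.
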